## Methods/design

### Design

The protocol is for a randomized, single-center feasibility trial comparing the prenatal MBSR program as an add-on to usual care with usual care alone. Participants will be randomized in a 1:1 ratio to an intervention or waitlist control group. A completed SPIRIT checklist is available in Additional Files and the study flow is outlined in Fig. 1. Self-report measures will be collected at three time points: (1) at baseline prior to randomization, (2) immediately after completion of the prenatal MBSR program, and (3) 3 months post-completion. Participants in the waitlist control group will be offered participation in a MBSR program after completion of the study.

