### Criteria for discontinuing allocated interventions

The criteria for discontinuation of study participation are (1) if requested by the participant, and (2) if the participant is absent from the prenatal MBSR class for two consecutive sessions and does not respond to email or phone calls.

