
#### Instructor qualifications

The prenatal MBSR program will be delivered by two highly trained MBSR teachers from the Danish Center for Mindfulness, Aarhus University. Both have been involved in the process of adapting the MBSR program to the present context and have extensive clinical psychiatric experience.

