### Primary outcome: feasibility of a full-scale RCT

The primary outcome of the study is to access the feasibility of a full-scale RCT, including accessing acceptance of trial participation among psychosocially vulnerable pregnant women. Acceptance of trial participation includes recruitment rate, acceptance of allocated interventions, compliance (i.e., attending ≥ 5 sessions), non-completion, and adverse events.

The recruitment process will be systematically registered in close collaboration between the Danish Center for Mindfulness, Aarhus University, and the outpatient clinic at Copenhagen University Hospital. Project meetings, every other week, will provide an opportunity for continuous evaluation of the recruitment process.

Prenatal MBSR class attendance will be registered at each session, and participants will be asked to notify the teacher in case of non-participation. Participants canceling two consecutive sessions will be contacted by phone, and the responsible midwife will be informed in order to provide support and prevent dropout. Adherence and acceptability of the prenatal MBSR program will be evaluated after the trial is finalized by examining attendance, time spent on home practice, and overall satisfaction with the program. On a daily basis, participants will be asked to register time spent on home practice. Satisfaction with the program will be evaluated at the last session. The prenatal MBSR teacher will register any adverse event ascribed to the prenatal MBSR program and notify the responsible researcher.

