### Scientific ethical considerations

Participation in a mindfulness-based program has not been associated with major side effects when the program is delivered by a certified teacher. The Danish Center for Mindfulness, Aarhus University, is affiliated with the Center for Mindfulness at Brown University and collaborates on setting international standards for education and teacher training. In the present study, a psychiatrist and a psychologist will be teaching the prenatal MBSR program. Both have extensive clinical experience and are certified mindfulness teachers. Some side effects have been reported in connection with mindfulness training, such as aggravation of symptoms that could be due to the increased focus on internal states and feelings of losing oneself. If any adverse events should occur, the teachers have the relevant expertise to ensure participant safety or referral to relevant treatment elsewhere. Both teachers are available for individual sessions between the program sessions. Any side effects related to the intervention will be systematically registered by the responsible researcher and published with the results of the study. The possible benefits of mindfulness training in pregnancy as described in earlier sections thus outweighs the potential side effects of the intervention. Moreover, there is a need for more evidence-based, non-pharmacological options for addressing prenatal mental healthcare needs in vulnerable groups for the benefit of both mother and fetus. The adaptations made to the original MBSR program require more research in order to establish an evidence base for the prenatal MBSR program, which is initiated with this feasibility study.

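### Adverse events are part of the primary outcome but are recorded only when attributed to the program, so recorded events have no control-arm rate and events in women who stop attending may be under-recorded

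*Protocol article*

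**What the plan says.** The section on the primary outcome includes adverse events: "Acceptance of trial participation includes recruitment rate, acceptance of allocated interventions, compliance (i.e., attending ≥ 5 sessions), non-completion, and adverse events". The same section states how they are captured: "The prenatal MBSR teacher will register any adverse event ascribed to the prenatal MBSR program and notify the responsible researcher".

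The section Scientific ethical considerations has a second statement: "Any side effects related to the intervention will be systematically registered by the responsible researcher and published with the results of the study". It also names the kind of harm reported with mindfulness training, "such as aggravation of symptoms that could be due to the increased focus on internal states and feelings of losing oneself".

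On the teachers, Instructor qualifications says: "Both have been involved in the process of adapting the MBSR program to the present context".

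On the control arm, Design says: "Participants in the waitlist control group will be offered participation in a MBSR program after completion of the study".

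On women who stop coming, the primary outcome section says: "Participants canceling two consecutive sessions will be contacted by phone, and the responsible midwife will be informed in order to provide support and prevent dropout". The discontinuation criteria cover a participant who requests it, and also apply "if the participant is absent from the prenatal MBSR class for two consecutive sessions and does not respond to email or phone calls".

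**The concern.** Both recording statements apply an attribution filter before an event enters the record. A usual-care woman cannot have an event attributed to a program she is not receiving, so the control arm is excluded by the rule itself. One component of the primary outcome of a randomised study then has no randomised comparator.

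This matters for the harm that the protocol names. The Setting section says that about 66% of referrals are supported by a psychiatric diagnosis. The Background says that earlier psychopathology and psychosocial adversity predict mental disorder during and after pregnancy. Some worsening without the program is therefore plausible, although the document gives no rate. Judging attribution case by case cannot separate that background from an effect of the program. A comparison between arms of all events, whatever their cause, can.

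The first step in the record is a teacher who helped adapt the program and who mainly sees women who attend. If symptom aggravation leads a woman to stop coming, her event is less likely to reach the log. A low count could then be carried into the planning of the full trial as reassurance that it does not provide.

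**Working it through.** The plan states no adverse-event figure, so there is none to reproduce. The check is a reading of the text, followed by arithmetic for scale.

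**1. Which women can generate a recorded event**

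| Source | Who registers | Which events | Usual-care women |
|---|---|---|---|
| Primary outcome section | Teacher, who notifies the researcher | Those ascribed to the program | Excluded by definition |
| Scientific ethical considerations | Responsible researcher | Those related to the intervention | Excluded by definition |

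The two rows can be read as one reporting chain. The attribution filter is present in both.

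**2. What else could reveal harm**

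- *Phone call to absentees.* It reaches women who cancel two consecutive sessions. Its stated purpose is support and retention, and non-responders meet a discontinuation criterion.
- *Symptom scales.* They are collected in both arms at baseline, after the program and 3 months later. Their recall windows are 7 days (EDS), one week (DASS-21), 14 days (WHO-5) and one month (PSS-10). The program has nine weekly sessions. Taking a month as about 4 weeks, the post-program questionnaire leaves roughly the first 9 − 4 = 5 weeks outside every one of these windows. An episode that began and resolved then need not show, and the scales as described do not ask about new treatment or hospital contact.

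**3. What a zero count would mean**

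Inputs: 60 women (Sample size) and 1:1 allocation (Design), so about 60 / 2 = 30 per arm. The exact two-sided 95% upper limit for 0 events in n women is 1 − 0.025^(1/n). For n = 30 this is 1 − 0.025^(1/30) = 0.1157, or **11.6%**. It bounds the rate of events that were both seen and attributed, which is not the rate of all adverse events.

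**4. How much could be lost from non-attenders (assumptions only)**

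Let *a* be the share not attending, *p₁* the event rate in attenders and *p₂* the rate in non-attenders. If no event in a non-attender were ever recorded, the share lost would be a·p₂ / [(1 − a)·p₁ + a·p₂]. With p₁ = 10%:

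- a = 10%, p₂ = 10%: 0.01 / (0.09 + 0.01) = 10%
- a = 30%, p₂ = 30%: 0.09 / (0.07 + 0.09) = 56%

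These are worst cases, because they give the phone call and the midwife contact no credit. The document supplies none of the three inputs.

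**5. What recording in both arms would give**

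Approximate 95% half-width of a risk difference with 30 per arm and common rate p: 1.96·√[2p(1 − p)/30].

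| Assumed p | Half-width (percentage points) |
|---|---|
| 5% | ±11.0 |
| 10% | ±15.2 |
| 20% | ±20.2 |
| 30% | ±23.2 |

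At 5% only 0.05 × 30 = 1.5 events per arm are expected, so the normal approximation is rough there.

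**The case against.** The best defence is that the protocol watches for harm in more ways than the adverse-event sentence suggests. Absentees are phoned, and their midwife is informed. The teachers offer individual sessions between classes. Depression, anxiety, stress and well-being are measured in both arms and analysed by intention to treat, so worsening by arm can be partly estimated. Weeks at birth and birth weight are collected. Adverse events are one of five listed components, and no progression rule depends on their count. An article may also leave adverse-event forms to the full protocol.

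Much of this stands, and it rules out four stronger readings that a reader might infer:

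- *Only the teacher records events.* The ethics section also gives registration to the responsible researcher. The two statements are compatible with a chain from teacher to researcher, so this is an ambiguity and not a clear contradiction.
- *Harm in women who stop attending is missed.* The phone call, the midwife contact and the questionnaires are routes by which it could surface. The text supports no more than possible under-recording.
- *No between-arm information on harm exists.* That is true of logged adverse events. It is not true of symptom scores.
- *A zero count hides a true rate of a particular size.* Any such figure needs a capture rate, and the document gives none.

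The defence does not remove the core point. None of these routes is described as adverse-event ascertainment. The attribution limit is a rule that the article states twice, so it is more than a detail left to another document.

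**Conclusion.** The point holds in this limited form. As written, the adverse-event component of the primary outcome will be a count from one arm, filtered by attribution, and it will reach the record mainly through teachers who helped adapt the program. No control rate and no between-arm difference in recorded adverse events can be produced. Under-recording among non-attenders is possible, and its size is unknown.

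The 11.6% upper limit for 0/30 assumes 30 women in the intervention arm and applies to attributed events only. The conclusion about the missing comparator needs no numerical assumption, because it follows from the two recording statements and the usual-care control. If the full protocol already collects adverse events in both arms regardless of cause, what remains is to correct the article's wording.

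This is a recommended, inexpensive improvement. It is not a must-fix, since the study plans no formal testing and bases no decision on the adverse-event count.

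**What to change.** 1. Add the same short adverse-experience block to the post-program and 3-month REDCap questionnaires in both arms, for example worsening of symptoms, new psychiatric treatment and hospital contact. Ask about the whole period since the previous questionnaire, whatever the suspected cause and whether or not the woman attended.
2. Report counts by arm with exact 95% confidence intervals, and show relatedness to the program in a separate column.
3. Tabulate weeks at birth and birth weight by arm. Both are already collected under Baseline characteristics.
4. Keep the teacher's log as a supplement to the prompted questions.
5. Reconcile the primary outcome section with Scientific ethical considerations, so that one role is named as responsible for the record and the other as its source.

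The cost is an amendment and a slightly longer questionnaire. The study began in mid-January 2021, so women already past an assessment would lack the new items, and the report should state how many. The between-arm estimate will stay imprecise at this sample size. Its use is to describe both arms and to try out the procedure that the full trial will need.

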### Secondary feasibility outcome

The secondary feasibility outcome includes the possible effects of the prenatal MBSR program as estimated by self-report measures assessing stress, anxiety, depression, well-being, decentering, reflective functioning, mindfulness, and compassion. The questionnaire packet is built and managed via REDCap (Research Electronic Data Capture) hosted by Aarhus University. Reminders will be emailed after 1 week in case of non-response.

#### The Perceived Stress Scale

The Perceived Stress Scale 10-item version (PSS-10) is a global measure of stress [25]. The questions concern thoughts and emotions experienced within the past month such as “In the last month, how often have you felt that you were unable to control the important things in your life?” The response format ranges from “never” (= 0) to “very often” (= 4). Scores range from 0 to 40 with higher scores pointing to more perceived stress. The Danish consensus version of the PSS-10 can be used in clinical research settings and has good psychometric properties [26].

#### The Edinburgh Depression Scale

The Edinburgh Depression Scale (EDS) is a widely used screening questionnaire containing questions on how the respondent has felt in the past 7 days [27]. The questionnaire has 10 items scored 0–3 on each item yielding a maximum score of 30. A higher score points to more depressive symptoms, and a score of 11 has been suggested as the optimal cutoff for depression according to both DSM-5 and ICD-10 criteria [28]. The EDS has been validated as a screening instrument for prenatal and postpartum depression, showing good psychometric properties [29].

#### Depression Anxiety Stress Scales

The Depression Anxiety Stress Scales (DASS-21) [30] has three subscales designed to discriminate between depression, anxiety, and stress in the last week. The DASS excludes somatic items such as sleep disturbance, lack of energy, and poor concentration, which may not be valid markers in pregnancy or the postpartum period [31]. Each subscale of depression, anxiety, and stress includes seven items. Response to each item is rated on a 4-point Likert scale ranging from “never” to “very much/most of the time.” Scores are calculated for each subscale, and higher scores point to more symptoms of stress, anxiety, or depression. The DASS-21 has shown good psychometric properties when administered to young adults in non-clinical settings [32].

#### The World Health Organization – Five Well-Being Index (WHO-5)

The WHO-5 is a short and generic global rating scale measuring subjective well-being [33]. It consists of five statements, and the respondent is asked to rate how well each of the statements applies to him or her when considering the last 14 days. Each item is scored from 5 “all of the time” to 0 “none of the time.” Final scores range from 0 to 100 with higher scores representing greater well-being. The scale has adequate validity both as a screening tool for depression and as an outcome measure in clinical trials and has been applied successfully across a wide range of study fields [33].

#### Prenatal Reflective Functioning Questionnaire

Parental reflective functioning refers to the caregiver’s capacity to reflect upon his/her own internal mental experiences as well as those of the child [34]. The Prenatal Parental Reflective Functioning Questionnaire (P-PRFQ) is a recently developed, 14-item questionnaire for assessing early parental mentalizing capacity [4]. Responses are rated on a scale from 7 “strongly agree” to 1 “strongly disagree.” The raw scores range from 14 to 98 and the index sum from 1 to 7. Higher scores indicate higher prenatal mentalizing capacity. The P-PRFQ has shown good initial psychometric properties [4].

#### The Experiences Questionnaire: subscale for decentering

Decentering reflects the capacity to take a non-judgmental and accepting stance regarding one’s thoughts and emotions as opposed to identifying with them [35]. The decentering subscale, of the experiences questionnaire, consists of 11 items with responses ranging from 1 “strongly disagree” to 5 “strongly agree.” The total score ranges from 11 to 55 with higher scores indicating higher decentering. Initial support has been reported for the reliability and validity of the scale as a measure of decentering [35].

#### The Five Facet Mindfulness Questionnaire

The Five Facet Mindfulness Questionnaire (FFMQ) assesses five general facets of being mindful in daily life: observing, describing, acting with awareness, non-reactivity to inner experience, and non-judging of inner experience. Items are rated on a 5-point Likert scale ranging from 1 “never or very rarely true” to 5 “very often or always true.” Higher scores suggest higher levels of mindfulness. Previous studies have provided good support for the construct validity of the FFMQ; furthermore, four of the five facets (except for “acting with awareness”) have been found to be significantly correlated with meditation experience [36].

#### The Self-Compassion Scale

The Self-Compassion Scale measures the ability to have a healthy stand towards oneself that does not involve evaluations of self-worth [37]. The scale consists of 12 items, and responses are given on a 5-point scale from 1 “almost never” to 5 “almost always.” Higher scores indicate more self-compassionate behavior. The psychometric properties of the scale have been extensively evaluated [37].

#### Baseline characteristics

Baseline data on age, marital status, number of children, social support, working status, education, obstetric complications (e.g., gestational diabetes), current use of psychotropic medication, and prior and current history of a mental disorder or drug abuse will be collected. Assessment of health practices will include self-reports of level and type of habitual exercise, smoking, and alcohol. Information on time of birth (weeks) and birth weight will be collected postnatally.

### Sample size

The study will include a total of 60 participants. This sample size is justified based on the design and objectives of the study [38].

### Randomization

Eligible participants will be randomized in a 1:1 ratio to either prenatal MBSR + usual care or usual care alone using the REDCap randomization module hosted by Aarhus University. REDCap is a secure, web-based application designed to support data capture for research studies [39]. A data manager from Aarhus University, not otherwise involved in the study, programs the randomization algorithm. Inclusion and thus randomization will take place consecutively until the estimated number of participants is reached.

### Data analyses

Statistical analyses will be performed using SPSS for Windows (version 27; IBM Corp, Armonk, NY). Skewness, kurtosis, and visual inspection of normal Q-Q plots will be used to inspect normality. Descriptive statistics will be presented as mean and SDs or median and interquartile range (IQR) depending on the distribution of the continuous variables or as frequencies for categorical variables.

Recruitment, participation, and retention rates will be reported and presented in a CONSORT flow diagram [40]. Data collected on numbers of eligible participants recruited, numbers randomized, adherence to, and compliance with the intervention, as well as dropouts lost to follow-up, will be presented as percentages and used to inform the development of a full-scale RCT.

Acceptability of the intervention will be assessed by dropout rates, by computing the mean number of completed sessions, and time spent on at-home practices in the prenatal MBSR group. Participation in ≥ 5 sessions will be considered compliant with the program. A loss to 12-week follow-up analysis will be conducted for age, education, employment, history of a mental disorder, participation in < 5 sessions of the intervention, and pre-scores on the PSS-10 by means of t-test and chi-squared test (χ^2^). A loss to intervention analysis will be conducted for participants attending < 5 sessions of the intervention applying a similar approach.

Analyses of a possible effect of the intervention will be performed based on the intention-to-treat principle, meaning that all participants will be included in the analysis irrespective of their compliance with the intervention protocol. Lastly, an additional per-protocol analysis will be conducted. Since the study is not powered by formal hypothesis testing, only effect estimates and 95% CIs will be presented in accordance with the CONSORT criteria for reporting of feasibility or pilot studies [40].

Independent t-tests (or the non-parametric equivalent Mann-Whitney U) will be conducted to compare the pre- and post-questionnaire scores of the intervention and control groups. In case of skewed distributions in baseline variables, e.g., age and history of mental disorders, logistic regression analyses will be performed.

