### Inclusion and exclusion criteria

The aim of the study is to address prenatal mental care in psychosocially vulnerable women with no particular attention to any specific psychiatric diagnosis or other psychosocial vulnerability. However, there are some cases where MBSR is not suited, which is specified in the exclusion criteria.

The following are the inclusion criteria:
Estimated due date no sooner than 3 months from the start of the intervention. The adapted MBSR program includes nine weekly sessions, and these criteria were included in order for the women to be able to complete the intervention.Eighteen + years of age.Speak and write Danish.Available for group intervention scheduled sessions. Being unavailable for two or more sessions is a reason for exclusion from study participation.Written informed consent to study criteria.

The following are the exclusion criteria:
Concurrent substance abusePsychotic disorders and post-traumatic stress disorderSuicidality

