The prenatal MBSR program has been pretested in five groups of pregnant women referred to the outpatient clinic. There was a maximum of 15 participants in each group. A psychiatrist and a psychologist with extensive clinical experience and MBSR teaching experience taught the groups. A midwife or a psychologist, from the outpatient clinic, participated in each of the groups. Pre- and post-self-report measures were collected. Attendance and dropout rates were systematically registered. Subsequent individual interviews with the participants and participating staff resulted in some adjustments to the program. In sum, the developmental process resulted in the following adaptations to the standard MBSR program: The first adaptation is that the prenatal MBSR program consists of nine 2-h sessions and no full-day  session. The rationale for including shorter sessions and no full-day sessions is to make the program more adaptable for the clinical context that it is intended for. The second adaption relates to the fact that transition to motherhood is often presented as an exciting and joyful time with naturally developing emotional growth by modern society and the media [24]. The idealistic image may not be a close representation of the actual experience for women with mental health or severe psychosocial problems. Therefore, the program emphasizes a particular focus on the mother-child relationship by drawing attention to the bodily sensations, emotions, and thoughts associated with pregnancy and motherhood as they unfold. The third adaptation includes a yoga program that is suitable for pregnancy. , The fourth includes shortened sitting meditations  and greater alternation, during sessions, between meditation exercises in order to accommodate the bodily changes associated with pregnancy. The fifth adaptation includes a reduced 15-min daily mindfulness practice, with options for longer practice; this is to make it more manageable considering the vulnerabilities and life circumstances of these women. Lastly, the sixth adaptation to the program is that it is delivered in a combination of physical attendance (sessions 1, 4, and 9) and online delivery. Combining physical attendance with online delivery reduces traveling time and ensures attendance. This is while still providing a good starting point for establishing a learning environment and the feeling of being part of a group. Online booster sessions will be offered every 3 months after finalizing the 9-week program and continues throughout the first postnatal year. Mothers are invited to bring their babies to the booster sessions thereby making it an opportunity to practice being mindful with their babies.

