#### Usual care (TAU)

Standard clinical practice, usual care (TAU), consists of routine pregnancy visits to the outpatient antenatal clinic at Copenhagen University Hospital, Amager and Hvidovre, and to a general practitioner. A multidisciplinary approach involves primarily preventive counseling by midwives and, in some cases, consultations with a physician or social worker throughout the pregnancy and follow-up until the early post-partum period. In some cases, usual care may include consultations with a psychologist, although usually limited to a few sessions, and in more severe cases, referral to psychiatric treatment. All consultations are individual, and the first session is planned in gestational week 18, with an average of six following consultations. Additional consultations are planned if deemed necessary.

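### MBSR is taught in classes and usual care is individual, yet all women are analysed as independent: if outcomes within a class are positively correlated, the post-treatment and 3-month 95% CIs will be too narrow.

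*Protocol article*

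**What the plan says.** - **Size and allocation.** "The study will include a total of 60 participants" (Sample size). Under Randomization, "Eligible participants will be randomized in a 1:1 ratio to either prenatal MBSR + usual care or usual care alone". The unit of randomization is the woman, so about 30 women go to each arm.
- **MBSR arm.** Women must be "Available for group intervention scheduled sessions" (Inclusion and exclusion criteria), and "the prenatal MBSR program consists of nine 2-h sessions and no full-day" day (The prenatal MBSR program). Class size is given only for the pretest: "There was a maximum of 15 participants in each group". The number and size of classes in the trial itself are not stated.
- **Control arm.** "All consultations are individual" (Usual care (TAU)).
- **Analysis.** Data analyses names independent t-tests, or Mann-Whitney U, for comparing the questionnaire scores of the two arms. The inferential output on effects is limited: "Since the study is not powered by formal hypothesis testing, only effect estimates and 95% CIs will be presented".

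No section mentions a class effect, clustering or an ICC.

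**The concern.** Women in one class go through nine sessions together. The section on the program presents the sense of belonging to a group as something the in-person sessions are meant to create. Shared group process is therefore a plausible source of correlation among classmates after treatment, and it has no counterpart in the control arm. This is a partially nested design. An independent-samples analysis takes the variance of the MBSR mean to be that of 30 unrelated women, which is too small if the correlation is positive.

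Two things are at stake. The CIs are the only inferential statement the plan will publish on effects, so a CI that overstates precision spoils the main thing a reader takes from that part. The study is also meant to inform a fully powered RCT, and planning that overlooks a class effect would give too small a trial.

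**Working it through.** **Is there a figure to reproduce?** No. The total of 60 comes without an effect size, SD, power or precision target, only the statement that "This sample size is justified based on the design and objectives of the study" with a literature reference. The check below concerns the precision of the planned analysis.

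**Inputs from the protocol:** 60 women, 1:1, so n = 30 per arm; MBSR in classes; individual control care; independent-samples analysis; 95% CI, taken as two-sided.

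**Assumptions (not in the protocol):** class size m from 5 to 15, that is six to two classes for 30 women; ICC of 0.01, 0.05 and 0.10; equal total variance in both arms; no dropout; equal class sizes.

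**Step 1, planned interval.** In SD units, SE = sqrt(2/30) = 0.258. With t(58 df) = 2.002, the half-width is 2.002 x 0.258 = 0.517 SD.

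**Step 2, class effect in the MBSR arm only.**
- Design effect: DE = 1 + (m - 1) x ICC.
- Variance ratio for the difference: (DE + 1)/2, because only one arm is inflated.
- True SE / planned SE = sqrt((DE + 1)/2).

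Example, two classes of 15 at ICC 0.05: DE = 1 + 14 x 0.05 = 1.70; variance ratio (1.70 + 1)/2 = 1.35; SE ratio sqrt(1.35) = 1.16.

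**Step 3, coverage of the planned 95% CI,** by simulation with 50,000 replicates per setting:

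| Classes x size | ICC | DE | SE ratio | Half-width with design effect (SD) | Coverage of planned CI |
|---|---|---|---|---|---|
| 6 x 5 | 0.01 | 1.04 | 1.01 | 0.522 | 94.9% |
| 6 x 5 | 0.05 | 1.20 | 1.05 | 0.542 | 94.1% |
| 6 x 5 | 0.10 | 1.40 | 1.10 | 0.566 | 92.7% |
| 3 x 10 | 0.01 | 1.09 | 1.02 | 0.528 | 94.5% |
| 3 x 10 | 0.05 | 1.45 | 1.11 | 0.572 | 92.6% |
| 3 x 10 | 0.10 | 1.90 | 1.20 | 0.622 | 89.6% |
| 2 x 15 | 0.01 | 1.14 | 1.03 | 0.535 | 94.2% |
| 2 x 15 | 0.05 | 1.70 | 1.16 | 0.601 | 90.8% |
| 2 x 15 | 0.10 | 2.40 | 1.30 | 0.674 | 86.4% |

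With ICC 0, simulated coverage is about 95% at every class size. The half-widths keep the 58-df multiplier.

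**Step 4, would a full partially nested model be practical?** Satterthwaite df = (a + b)^2 / (a^2/(k - 1) + b^2/29), with a = DE/30, b = 1/30 and k classes. At ICC 0.05:
- Two classes: a = 0.0567, b = 0.0333; df = 0.00810/0.00325 = 2.5; t = 3.58; SE = sqrt(0.0900) = 0.300; half-width 1.07 SD, or 1.07/0.517 = 2.1 times the planned one.
- Three classes: a = 0.0483; df = 5.5; t = 2.50; SE = 0.286; half-width 0.71 SD, or 1.4 times.

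At ICC 0.10 with two classes the factor is 2.8. With so few classes the ICC itself could not be estimated usefully.

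**Step 5, effect on a later trial.** By the same ratio, a full trial with classes of 15 that omits the class effect would need its size multiplied by 1.35 (ICC 0.05) or 1.70 (ICC 0.10).

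**The case against.** The strongest reply is that the effect may be trivial. The protocol gives no ICC, and at 0.01 the planned intervals are close to nominal. The 15 is a pretest maximum, so two classes of 15 is the extreme case. Women are recruited at about 18 to 24 weeks and randomized consecutively, and the due date must be at least 3 months after the start. Classes may therefore have to be filled quickly, which favours smaller and more numerous ones. This stands, and it is why the range runs to six classes and the conclusion is conditional.

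A reader might infer more than the documents support in four ways:

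- **That the CIs are certain to be too narrow.** This needs a positive ICC, which the protocol neither states nor rules out.
- **That shared teachers or calendar time drive the correlation.** Two teachers are named for the whole program; if the same pair takes every class, teacher adds no variance between classes, and the documents do not settle this. Controls are randomized over the same period, so time effects reach both arms. Group process is the firmer ground.
- **That the full RCT will be sized from this trial's SD or CIs.** No section says so. Data analyses ties the recruitment, adherence and dropout percentages to the design of the full trial.
- **That the plan should have estimated the variance between classes.** With two or three classes the estimate would be too imprecise to use.

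It is also fair to say that feasibility is the primary outcome, that efficacy is exploratory without hypothesis tests, and that a half-width of 0.52 SD already supports no firm efficacy claim. This lowers the priority. It does not make an interval labelled 95% right when its coverage may be lower. Nor is this a detail left to an analysis plan: the protocol itself names the independent-samples methods.

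**Conclusion.** The concern holds in conditional form. The named analysis does not match the way treatment is delivered, and any positive correlation within classes makes the CIs for the post-treatment and 3-month differences too narrow. Baseline scores are collected before randomization and are unaffected, as are the point estimates and all feasibility percentages.

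The size ranges from negligible (ICC 0.01, or small classes with a low ICC) to material (coverage of 86% with two classes of 15 at ICC 0.10). It rests on assumed class sizes and ICCs, with 30 women per arm and equal variances. The priority is minor to moderate, because efficacy is a secondary aim.

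**What to change.** 1. Record class membership for each woman in the MBSR arm, and report the number and size of classes. Attendance is already registered at each session, so this adds little work.
2. Keep the planned effect estimate. Beside each planned CI for the post-treatment and 3-month differences, present one with the MBSR-arm variance multiplied by 1 + (m - 1) x ICC at ICC 0.01, 0.05 and 0.10. State that the planned CI assumes no class effect, and label the ICCs as assumed values.
3. Fit a partially nested model (random class effect in the MBSR arm only, small-sample df) only if there are enough classes for a stable fit. With two or three classes it would widen the interval about 2.1-fold or 1.4-fold at ICC 0.05 and would give no useful ICC.
4. State that any sample size for the full RCT will include a design effect for the MBSR arm.

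The cost is one recorded variable, revised analysis wording, a little more analysis, and wider secondary, exploratory intervals. Nothing changes in recruitment, treatment or the number of women.
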